### Randomization

To ensure balanced comparability between groups, we will use SPSS software (version 25.0; IBM Corp) to generate a random sequence, and 42 participants with VCI who meet the inclusion criteria will be randomly assigned to the acupuncture and control groups at a ratio of 1:1. In addition, the 42 numbered random sequences as well as the grouping scheme will be placed independently in sealed opaque envelopes, which will be opened only when a patient with VCI is enrolled. The randomization and concealment processes described earlier will be carried out by an independent third-party statistician who is not involved in any subsequent parts of this study.

### Blinding

Because of the limitations of the protocol and the specific nature of acupuncture treatment, it will not be possible to blind the participants and the acupuncturists. However, to improve the quality and reliability of this study, the researchers will be blinded during the efficacy assessment, data collection and management, and statistical analysis of the results. Thus, the efficacy assessors, data collection and management personnel, and outcome analysis personnel will not be aware of the grouping of the trial and will not be allowed to communicate with each other or with the participants about the treatment. In addition, to prevent bias in the results by nonblinded participants or researchers, this study will only involve individuals who do not have a conflict of interest or preconceived position.

### Intervention

#### Overview

Different groups will receive different interventions: the acupuncture group will receive acupuncture in addition to conventional medical treatment and cognitive rehabilitation training, the control group will receive conventional medical treatment and cognitive rehabilitation training only, and healthy participants will not receive any treatment. All of the above treatments will be performed by physicians and therapists who are certified and have more than 5 years of clinical experience. Below we describe the specific interventions for the 2 intervention groups.

#### Acupuncture Group

On the basis of conventional medical treatment and cognitive rehabilitation training, we will use Shenting and Baihui for electroacupuncture treatment. The specific acupuncture point positioning standards refer to *Acupuncture and Moxibustion* (“14th Five-Year Plan” National Higher Education Planning Textbook for the Chinese Medicine Industry). The specific method is as follows: the patient is placed in a supine position, and after routine disinfection of the Shenting and Baihui points with 75% alcohol cotton balls, the patient is stabbed backward with Hua Tuo brand (0.25 mm×25 mm) acupuncture needles in a flat direction (needle body and skin surface layer 15 degrees) of Baihui 0.8 to 1.0 inch and Shenting 0.5 inch. The electroacupuncture therapy instrument (SDZ-II; Jiangsu Medical Supplies Co) is connected to acupuncture needles after the patient gets qi (local soreness), and the waveform is continuous for the first 15 minutes, at an intensity that is tolerated by the patient, and then changes to a sparse waveform after 15 minutes to prevent electrical adaptation. After 30 minutes of electroacupuncture, the electroacupuncture instrument is removed; the needles are not removed and are retained for 1 hour. Cognitive function training is performed during the retention period, and the needles are twisted once at the beginning and once at 30 minutes, until the end of cognitive function training. The acupuncture needles are then removed. The electroacupuncture treatment will be performed once a day, 6 times a week, for 4 weeks.

#### Control Group

The control group will receive only conventional medical treatment as well as cognitive rehabilitation training. Specific treatment will include symptomatic treatment for the patient’s underlying diseases, such as controlling blood pressure, blood sugar, and blood lipids, antiplatelet aggregation, and nourishing brain cells. At the same time, according to the patient’s condition, a combination of manual training and computer training will be used to perform conventional cognitive function training such as category classification, rule (response) inhibition, plan analysis, reasoning and comprehension, working memory, and synthesis ability, for 1 hour per session, 6 times a week, for 4 weeks.

#### Healthy Control Group

The healthy control group will receive no intervention.

### Outcome Measurements

#### Overview

The 3 main areas of assessment will include neuropsychological tests, SWI, and serum iron metabolism. Researchers who are blinded to the treatment allocation will carry out all treatment evaluations.

#### Neuropsychological Tests

Cognitive function will be assessed at baseline and after 4 weeks of treatment by a professional evaluator using neuropsychological tests, and the evaluator will not be aware of the current grouping. The following are the neuropsychological test scales that will be used in this experiment.

#### MMSE Scale

The MMSE scale consists of 30 questions (1 point per question) in 7 areas: temporal orientation, place orientation, immediate memory, attention and calculation, delayed memory, language, and visuospatial ability [25]. Scores on this scale are closely related to literacy level, and it is generally accepted that people with illiteracy (≤17), primary school education (≤20), and junior high school and above education (≤24) have different degrees of cognitive dysfunction. Because of its simplicity, time-saving features, convenience of administration, and wide range of applications, the MMSE scale is used for the initial screening of different types of cognitive impairment and dementia.

#### MoCA Scale

The MoCA scale was developed by Tsai et al [26] in 2004 for rapid screening of mild cognitive impairment and has better sensitivity than the MMSE. The MoCA scale assesses cognitive domains including attention and concentration, executive function, memory, language, visual-structural skills, abstract thinking, numeracy, and orientation, with a total scale score of 30, and test results showing a normal value of ≥26.

#### Clinical Dementia Rating

In Clinical Dementia Rating, the physician obtains information by talking to the patient and family to quickly complete an assessment of the patient’s level of cognitive impairment [27]. The scale’s assessment domains include memory, orientation, judgment and problem-solving, work and social interaction, family life and personal hobbies, and independent living skills. Each of the above 6 functions was evaluated at 5 levels, from no impairment to severe impairment. The 6 abilities were combined into a total score that is based on the overall scoring criteria, with the results expressed as 0, 0.5, 1, 2, or 3, which are considered to represent normal, suspicious, mild, moderate, and severe dementia, respectively.

#### Serum Iron Metabolism–Related Indicators

A total of 4 mL of blood will be collected from patients in the morning on an empty stomach. The supernatant will then be extracted after centrifugation at 3000 revolution/min for 15 minutes at 4 °C. The levels of iron, ferritin, transferrin, transferrin receptor 1, total iron binding capacity, and hemoglobin will be measured using enzyme-linked immunosorbent assay.

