### Trial Design and Setting

The proposed protocol involves a randomized controlled clinical trial to investigate whether Tongdu Xingshen acupuncture can improve the clinical performance of patients with VCI by regulating brain iron deposition and body iron metabolism. In total, 42 patients with VCI hospitalized at the First Affiliated Hospital of Henan University of Traditional Chinese Medicine from May 2023 to December 2025 and 21 healthy participants will be included in the study. Participants will be divided into acupuncture, conventional treatment, and healthy control groups according to a ratio of 1:1:1, with 21 participants in each group. The control group (n=21) will receive conventional medical and cognitive rehabilitation treatment, the acupuncture group (n=21) will receive professional acupuncture treatment by a professional acupuncturist on the basis of the conventional treatment, and the healthy control group (n=21) will not receive any intervention. All of the above treatments will be performed for 4 weeks, 6 times per week. Brain iron deposition and serum iron metabolism will be measured at week 0 (baseline) and week 4 of treatment using SWI and blood biochemistry. In parallel, a neuropsychological test battery including the Mini-Mental State Examination (MMSE), Montreal Cognitive Assessment (MoCA), and Clinical Dementia Rating will be administered to evaluate comprehensive cognitive function and clinical symptoms. Details of the proposed study process are presented in Figure 1 and Table 1.

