### Safety Evaluation and Adverse Events

We will minimize the occurrence of adverse events in this clinical trial to ensure the safety of each participant. A comprehensive physical safety examination will be performed on all volunteers before and after treatment, including vital signs (heart rate, blood pressure, and respiration), routine blood and urine tests, biochemical function tests, electrocardiography, and liver and kidney function tests. Possible adverse reactions in this study include pain during acupuncture, fainting, and skin breakage or other injury caused by improper handling. If the patient experiences acupuncture fainting because of weakness or excessive stress, the acupuncture treatment will be stopped immediately, and the patient will be placed in a comfortable position and given warm water until they recover. In addition, if pain or systemic adverse reactions are caused by excessive current and voltage intensity, the electroacupuncture instrument will be turned off immediately. After confirming that the patient has no adverse reactions, the electroacupuncture instrument will be properly connected and used correctly according to the operational requirements. We will not only record the occurrence of any of the abovementioned adverse events in the case report book but will also actively deal with them.

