### Statistical Analysis

All data will be statistically analyzed by professional statisticians using SPSS software (version 25.0). If the data involved satisfy the characteristic properties of a normal distribution with uniform variance, we will use the mean and SD to describe them; conversely, if the data are not normally distributed, we will use the median and IQR to describe them. All statistical results will be considered statistically significant at *P*<.05.

Neuropsychological scale scores, iron metabolism–related indicators, and brain iron deposition are all measurement data. Normally distributed data with uniform variance among 3 groups will be analyzed using 1-way ANOVA, followed by multiple comparisons using the least significant difference test, whereas those with nonnormal distributions will be compared using the Kruskal-Wallis test followed by the Mann-Whitney *U* test with Bonferroni correction. Correlations between neuropsychological scale scores and serum iron metabolism indexes and brain iron deposition in patients with VCI will be assessed using Pearson correlation analysis.

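### Serum iron and total iron binding capacity are assigned to ELISA, which cannot measure the first or directly measure the second, so two of the six serum indicators have no valid assay as written

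*Protocol article*

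**What the plan says.** The section Serum Iron Metabolism–Related Indicators describes a 4 mL fasting blood sample. On processing it says: "The supernatant will then be extracted after centrifugation". It then assigns one method to six analytes: "The levels of iron, ferritin, transferrin, transferrin receptor 1, total iron binding capacity, and hemoglobin will be measured using enzyme-linked immunosorbent assay".

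Only one other place describes how these indicators are obtained. Trial Design and Setting says that "serum iron metabolism will be measured at week 0 (baseline) and week 4 of treatment using SWI and blood biochemistry". It names no assay for any single analyte.

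Safety Evaluation and Adverse Events lists "routine blood and urine tests, biochemical function tests, electrocardiography, and liver and kidney function tests" before and after treatment. This is for safety monitoring, and neither iron nor binding capacity is mentioned there.

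The indicators matter to the trial. The Overview of Outcome Measurements states: "The 3 main areas of assessment will include neuropsychological tests, SWI, and serum iron metabolism". Research Objectives makes body iron metabolism part of the second primary objective. Statistical Analysis treats the indicators as measurement data for group comparison and also plans "Correlations between neuropsychological scale scores and serum iron metabolism indexes and brain iron deposition in patients with VCI".

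**The concern.** An outcome is only as good as the match between the assay and the quantity it is meant to measure. Here one immunoassay statement covers six quantities of different kinds. An enzyme-linked immunosorbent assay works by antibody capture of an antigen. Iron is not such a target, and binding capacity is not a molecule at all but the amount of iron that the serum can take up.

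If a laboratory followed the sentence literally, the values recorded under those two names would not represent iron or binding capacity. They would still enter the group comparisons and the correlations with cognitive scores. No choice of test can repair that at the analysis stage. What is at stake is part of the mechanistic question, whether acupuncture acts through body iron metabolism. The question whether cognition improves is not at stake.

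**Working it through.** No formula, power figure or effect size is involved. The check sets the named method against each named analyte and then looks for any other text that supplies a different method.

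**Step 1. Method against analyte**, from Serum Iron Metabolism–Related Indicators:

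| Indicator | What it is | Can an immunoassay target it? |
|---|---|---|
| Ferritin | protein | yes |
| Transferrin | protein | yes |
| Transferrin receptor 1 | protein | yes |
| Hemoglobin | protein | in principle yes, but see step 3 |
| Iron | metal ion | no |
| Total iron binding capacity | functional property | not directly |

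Indicators listed: 6. Indicators that are not antibody targets: 2. Share: 2/6 = 33%.

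**Step 2. Could binding capacity be obtained indirectly?** It can be calculated from a transferrin measurement, and transferrin is itself on the list. But the text lists transferrin and binding capacity as separate items, says that both are measured, and gives no conversion. That route is available to the sponsor but is not the stated one. Serum iron has no equivalent route through the listed proteins.

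**Step 3. Hemoglobin.** The method is possible, but the specimen is unclear. The sentence places hemoglobin among analytes read from the supernatant of centrifuged blood. There, hemoglobin would mostly reflect what has been released from red cells and not the blood hemoglobin level. It is not counted among the two, but any rewrite of the sentence has to deal with it.

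**Step 4. Is there an overriding statement elsewhere?** Trial Design and Setting gives only a general label for the blood work. Safety Evaluation and Adverse Events lists routine tests without naming iron or binding capacity. No section gives either analyte a method other than ELISA.

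**Step 5. What depends on the two indicators?** They belong to one of the three main assessment areas and to the second primary objective, and they enter the planned comparisons and correlations. The calculation under Sample Size uses MoCA means and SDs only, so it does not depend on them.

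**The case against.** The strongest reply is that the premise weakens the harm. If these two quantities cannot be run by ELISA, a competent laboratory would hardly have tried, and the likelier explanation is one condensed sentence that folds several methods into one. The general wording in the design section fits that reading. This stands as a limit on the claim: what is shown is a wrong method statement, not bad data. It does not remove the point, because the article gives a specific method rather than leaving one out, and nothing else in it corrects that method.

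A reader might be tempted further in several directions that the document does not support.

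- **That the trial's iron results are noise, or will give a false null or a spurious association.** This would require a mislabelled kit to be in actual use. Nothing says so.
- **That the design section contradicts the assay sentence and establishes colorimetry.** Blood biochemistry is a generic label. It neither excludes an immunoassay nor names a chemical method. The two sections need aligning, but this is not a clear contradiction.
- **That iron and binding capacity are the most direct measures of body iron metabolism.** The article does not rank the six indicators.
- **That the correct tests are already being run for safety, or that stored serum can be re-assayed.** The safety list does not include these two markers, and stored serum is not mentioned.
- **That a count of affected correlations measures the damage.** Three scales by six markers gives 18 pairs, of which 3 × 2 = 6 involve these two markers. But Statistical Analysis does not fix which pairs or time points will be tested, and a count says nothing about bias.

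It is also fair to say that the case is weaker for binding capacity than for iron, because of the transferrin route in step 2.

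**Conclusion.** The point holds in this form. As written, the assay statement cannot yield valid values for serum iron, and cannot directly yield binding capacity without a derivation that is not stated. That is 2 of 6 serum indicators (33%). It affects the serum part of the second primary objective and leaves the cognitive efficacy comparison, the sample size and the brain iron imaging untouched.

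The conclusion rests on the general definition of an immunoassay and on the sentence meaning what it says. If the sentence merges several methods, the fault is a misleading and non-reproducible method statement, and the text needs the same correction. The document does not allow any estimate of bias or lost precision, and none is claimed. It should be corrected, but it does not threaten the trial as a whole.

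**What to change.** In Serum Iron Metabolism–Related Indicators, replace the single assay statement with one method per analyte:

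- ferritin, transferrin and transferrin receptor 1: ELISA, as now;
- serum iron: a chemical assay, for example colorimetric;
- total iron binding capacity: a chemical assay, or an explicit calculation from transferrin with the formula given;
- hemoglobin: name the assay and the specimen, so that it is not left without a method.

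Align the wording in Trial Design and Setting with this list.

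Because up to 30 people had been enrolled by May 15, 2024, and recruitment was expected to run to June 2025, also confirm which method was used for samples already assayed. Report any iron or binding-capacity values obtained by ELISA as not validly measured, and keep them out of the comparisons and correlations.

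The cost is a few sentences of text and a modest reagent expense. The one real downside is that these two markers may be lost for some participants already sampled, if their values turn out to have come from an unsuitable assay.

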#### High-Resolution Magnetically SWI

All participants will undergo SWI, and the data will be postprocessed and analyzed using Susceptibility Mapping and Phase Artifacts Removal Toolbox software (The Math Works Inc) to obtain QSM images. Signal processing in Nuclear Magnetic Resonance software (Philips Healthcare Netherlands Ltd) will then be used to detect and quantitate the corrected phase value in the region of interest, including bilateral parietal cortex, frontal white matter, caudate nucleus, putamen, globus pallidus, thalamus, red nucleus, substantia nigra, hippocampus, and dentate nucleus [21,22,28]. Care will be taken to avoid blood vessels, calcifications, and visible lesions during the measurements. Each site will be measured twice, and the average of the 2 measurements will be taken. The magnitude of magnetization will be used to indicate the level of iron content of the tissue.

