Numerous studies have indicated that traditional Chinese medicine (TCM) can play an important role in the treatment of VCI [9,10]. In particular, acupuncture has the unique advantages of simplicity, convenience, safety, and effectiveness in the treatment of VCI [11]. According to the understanding of VCI in Chinese medicine, in which the “brain” and “governor vessel” play key roles in regulating the “vital spirit” and brain function, the “deficiency of the medulla oblongata and loss of the use of the spiritual mechanism” is considered to be the fundamental pathogenesis of VCI, leading to the development of the Tongdu Xingshen treatment principle. Several prior clinical studies in our laboratory and meta-analyses published by other researchers have demonstrated that acupuncture is effective in improving cognitive function and enhancing overall outcomes in patients with a history of stroke [12-14]. However, the in-depth mechanisms of Tongdu Xingshen acupuncture treatment for VCI require further validation and exploration.

The pathogenesis of VCI is complex. Previous studies of the pathogenesis of VCI have mainly focused on blood-brain barrier disruption, secondary inflammation, excitatory amino acid toxicity, cell autophagy, and apoptosis [15,16]. With the discovery of ferroptosis and the in-depth study of its mechanism of occurrence, more and more scholars believe that it plays an important role in central nervous system diseases [17,18]. By exploring the relationship between serum iron metabolism, brain iron deposition, and cognitive impairment, researchers in various countries, including China, have found that iron deposition can lead to the development of inflammation, abnormal protein aggregation, and degeneration in the central nervous system, which in turn causes a progressive decline in cognitive function [19,20].

Quantitative susceptibility mapping (QSM) is a postprocessing technique developed in recent years on the basis of sensitivity-weighted imaging (SWI), which enables to quantify the magnetic susceptibility properties of tissues in vivo [21,22]. The ability to measure brain iron content, which is quantified by the magnetization rate values obtained from QSM calculations, raises the possibility of investigating ferroptosis in VCI.

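### Two iron read-outs need correcting: regional brain iron is named both as QSM susceptibility and as corrected phase, and hemoglobin is assigned to ELISA on centrifuged supernatant

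*Protocol article*

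**What the plan says.** **Brain iron.** The Introduction presents QSM as a way to quantify magnetic susceptibility in vivo and says that brain iron content is "quantified by the magnetization rate values obtained from QSM calculations". In the section High-Resolution Magnetically SWI, the scans are first postprocessed "to obtain QSM images". A second software package is then "used to detect and quantitate the corrected phase value in the region of interest", followed by a list of 10 regions. The section closes: "The magnitude of magnetization will be used to indicate the level of iron content of the tissue".

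**Blood.** The section Serum Iron Metabolism–Related Indicators describes one 4 mL fasting draw. "The supernatant will then be extracted after centrifugation", and the analyte list that follows starts with iron, ferritin, transferrin and transferrin receptor 1 and ends "total iron binding capacity, and hemoglobin will be measured using enzyme-linked immunosorbent assay". No other fraction or tube is mentioned there. Under Safety Evaluation and Adverse Events, all volunteers have an examination before and after treatment that includes "routine blood and urine tests, biochemical function tests". That examination is not linked to the iron outcomes.

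**The concern.** Each point concerns a procedure that the article states, so neither is a matter of detail left out.

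For imaging, the quantity said to represent iron is not the quantity said to be read in the regions. If the read-out sentence is followed, the variable that reaches the database is not the one the Introduction defines, and the QSM step that precedes it serves no purpose. If the definition is followed, the read-out sentence is wrong. One of them has to change before the regional values are analysed.

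For blood, the specimen and the analyte do not match. Hemoglobin is carried in red cells, and centrifugation separates these from the supernatant. A value obtained this way would be reported under the name of hemoglobin without being the patient's hemoglobin concentration.

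Both variables matter to the trial's question. The second of the two primary objectives asks whether acupuncture acts through iron in brain and blood. The Statistical Analysis section compares these measures between groups and correlates them with the cognitive scores.

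**Working it through.** The point is about what is measured, so there is no figure in the plan to reproduce. The check sets the statements side by side.

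**1. Brain iron**

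| Place | Quantity named |
|---|---|
| Introduction | magnetization rate from QSM, i.e. susceptibility |
| SWI section, postprocessing step | QSM images |
| SWI section, regional read-out step | corrected phase |
| SWI section, closing sentence | magnitude of magnetization |

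Three of the four entries point to susceptibility. The one that differs is the only one that tells the operator what to extract per region. Phase reflects the local magnetic field, and QSM is the step that turns field information into tissue susceptibility, so the two terms are not interchangeable. The article gives no conversion from one to the other.

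**2. Hemoglobin**

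- Specimen: supernatant after centrifugation.
- Assay: ELISA, named once for all six analytes.
- Inference: red cells are not in the supernatant, so only hemoglobin free in that fraction can be assayed.
- Other possible source: the routine blood test in the safety examination, which is not assigned to this outcome.

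**3. Extent**

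- Regions: parietal cortex, frontal white matter, caudate nucleus, putamen, globus pallidus, thalamus, red nucleus, substantia nigra, hippocampus and dentate nucleus = 10. If bilateral applies to every one, 10 × 2 = 20 values per scan.
- Baseline assessments: 42 patients + 21 healthy controls = 63.
- Follow-up assessments: 42, because the Abstract plans re-evaluation only for the two patient groups.
- Total: 63 + 42 = 105 assessments.
- Blood markers affected: hemoglobin only, 1 of 6.

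These counts show where the two definitions apply. They do not measure an error in any result. The documents hold no data on how far phase and susceptibility differ in these regions, so no such size can be given.

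**The case against.** The strongest reply on imaging is that corrected phase is simply a loose term for the QSM value. The regional reading comes after the QSM step, the closing sentence names magnetization as the iron indicator, and the Introduction agrees. This is plausible, and it means nobody can say that phase will certainly be analysed. It does not remove the need to correct the sentence, because as it stands it instructs the reader to extract something else.

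On blood, the reply is that a short laboratory paragraph in a journal article groups six analytes under one method and leaves sample handling per analyte to the full protocol. The Trial Design and Setting section speaks of blood biochemistry, and a routine blood test is planned anyway. That may well be how hemoglobin is obtained in practice. If so, the statement in the serum section is wrong and should say so: condensing explains what is missing, but here a fraction and an assay are stated.

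A reader might also infer more than the text supports:

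- That the two read-outs would disagree in direction, or are offered as alternatives to choose between after the data are seen. The documents give no data on the former, and the closing sentence of the SWI section does name one indicator.
- That brain iron is the main mechanistic outcome. The objective pairs it with body iron metabolism, and the outcome overview lists three areas without ranking them.
- That the absence of measurement units, a reference region or a rule for combining left and right is part of the fault. An article commonly leaves these to the full protocol.

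**Conclusion.** The point holds as two specification faults. The regional brain-iron variable is named inconsistently, possibly by a slip of wording, and read literally the wrong variable is extracted. Hemoglobin is assigned to a specimen that, as written, yields only free hemoglobin.

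The conclusion rests on three assumptions: that magnetization rate and magnitude of magnetization both mean QSM susceptibility, which the Introduction's description of QSM supports; that phase and susceptibility are distinct quantities; and that centrifugation removes red cells from the supernatant. The last two are general technical knowledge and are not stated in the article.

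The faults should be corrected because the variables carry the second primary objective and enter the group tests and correlations. They do not touch randomization, safety, the cognitive outcomes or the sample-size calculation, which is based on the MoCA. Nothing here calls the other five blood markers into question.

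**What to change.** - **SWI section:** name the regional QSM susceptibility value as the single brain-iron outcome, in the same term as the Introduction. Delete corrected phase, or label it a secondary or sensitivity read-out.
- **Serum section:** remove hemoglobin from the list of analytes measured by ELISA on supernatant, and state that it is taken from the routine blood test planned before and after treatment. Confirm that this test covers the healthy controls at baseline, since they receive no treatment.

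The cost is mainly wording. If regions have already been read as phase, they need to be re-read on the QSM maps that the plan already produces. Hemoglobin should need no new sample, on the assumption that the routine blood test reports it. Both changes should be made before the database is locked.
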